**Discussion:**

The study aims to assess the changes in, for example, psychological wellbeing, career efficacy and hopefulness, that occur as a result of participation in a high support intervention vs routinely available support. The results will help to inform policy and practice by indicating whether a therapeutic approach to job-seeking support is more effective for long-term unemployed job-seekers than routinely available (and less therapeutic) support. The findings will also be important in understanding what works and for whom with regard to potentially undoing the negative psychological impacts of unemployment, building psychological capital and employability within the individual, and developing career trajectories leading to more sustainable employment.

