### Sample size

A power analysis was conducted using the primary outcome measure of overall psychological wellbeing (GHQ-12) in order to identify the minimum sample size required to detect an increase in wellbeing post intervention. As already indicated, the Pathways to Work activation model is a recently implemented approach and so no previous evaluations or comparable studies have been undertaken, although similar studies had been conducted in Sweden [51], France [52], Australia [6] the UK [41, 42] Finland [72] and the USA [53, 73]. Analysis of these studies indicate varying sample sizes (*n* = 16–1200); thus, to ensure the minimum sample size is achieved and the study is powerful enough to detect significant differences between the groups, a power analysis was performed to establish a realistic estimate based on the primary outcome measure. This analysis was conducted for an independent samples t-test, as this is expected to be the least powerful test in the overall main analysis. The analysis was two-tailed (alpha of 0.05), as we do not know in advance which group will perform better in GHQ-12 terms. G*Power t-test calculations for the difference between two independent means (two groups) show that for the current study, 128 unemployed participants (64 in each group) will be sufficient to detect a change of 0.50 (medium) at 80% power and at 5% significance at a given time point. An allowance of (approximately) 10% will be made for possible attrition, so the actual sample size target will be 70 per group. This should be more than sufficient for Mixed Model Repeated Measures (MMRM) across the three time points to have > 80% power and also allow for post-hoc t-tests both between groups and within groups to have ≥ 80% power.

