## Methods: assignment of interventions

### Allocation

#### Sequence generation and implementation

The participant’s initial appointment is with the researcher who explains the study and consent forms and administers the participant questionnaire. The researcher informs the data manager of those clients who agree to participate and who give informed consent. The data manager randomly assigns eligible participants to either the intervention or control group on a 1:1 basis using the SNOSE (sequentially numbered opaque sealed envelopes) method as described by Doig and Simpson [74]. Randomisation is conducted by the data manager only, ensuring that the randomisation is achieved without any influence from the researcher or the practitioners involved in the delivery of the service.

Seven practitioners deliver services to the intervention and control groups. Practitioners who deliver the intervention are not involved in delivering services to the control group (and vice versa) in order to ensure that practitioners deliver the service with fidelity and that there is no contamination between the intervention and control groups.

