In addition, descriptive statistical summaries (means, standard deviations, frequencies) will be presented for primary and secondary outcome measures at each time point (baseline, post intervention and six-month post intervention). Of most interest will be the identification of changes in primary and secondary outcome measures at group level between T0 (baseline) and T1, and T0 and T2, and between T1 and T2. Additional descriptive analysis (e.g. frequencies) of the re-employment (secondary) measure will be conducted to assess the differences between the two groups in terms of their re-employment outcomes.

Sub-group MMRM analysis will be conducted to investigate if the intervention effects differ for certain participant groups, based on variables such as gender, age, education level and unemployment duration. T-tests and Chi-squared tests will be employed to identify mean differences and associations with regard to primary and secondary outcome measures.

A full statistical analysis plan (SAP)—in the form of a Trials (free) update—will be provided once all data are gathered and before opening the database. Analysis will be conducted using SPSS software (IBM SPSS Statistics version 22).

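### The plan asks whether effects differ between groups but names only sub-group MMRM; if those models are compared by significance, a uniform 0.50 SD effect would look different in two equal halves about half the time

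*Protocol article*

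**What the plan says.** In the protocol article, Statistical methods/analysis states that "Sub-group MMRM analysis will be conducted to investigate if the intervention effects differ for certain participant groups". Four variables are offered as examples: gender, age, education and time unemployed. The list is open-ended, and no cut-points or split sizes are given. The same section brings age, gender, duration of unemployment and education into the main MMRM only as control variables. Nowhere does it mention a term crossing treatment with any of them. A full SAP is promised before the database is opened.

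The Discussion part of the abstract says the findings will matter for "understanding what works and for whom".

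The Sample size section powers only the overall comparison. It says the planned number "will be sufficient to detect a change of 0.50 (medium) at 80% power and at 5% significance at a given time point", and then: "An allowance of (approximately) 10% will be made for possible attrition, so the actual sample size target will be 70 per group".

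**The concern.** The question posed is one of effect modification: is the treatment effect in one group different from that in another? A model fitted within each group answers another question, namely how large the effect is there and whether it differs from zero. Two such answers can fall on opposite sides of the 5% line while the effects themselves are identical, because each half of the sample has much less power than the whole. Reading one significant and one non-significant result as a difference therefore has an error rate that depends on the true effect and the split, and it can be far above 5%.

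At stake are the statements about who benefits. The main policy claim is not at stake, because it rests on the overall comparison of the two arms.

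**Working it through.** **Inputs from the protocol article.** Two-sided 5% test, standardised difference 0.50, 80% power, 64 evaluable per group and 70 per group randomised (Sample size); allocation "either the intervention or control group on a 1:1 basis" (Sequence generation and implementation); four named variables (Statistical methods/analysis).

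**Assumptions not in the document.** Each variable splits the sample in two, in equal halves unless stated, with a range up to 80/20. The true effect is the same in both parts. As in the plan's own power calculation, the test is a t-test at one time point. Results are shown for 64 and for 70 per group.

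**Step 1: the plan's own figure.** The normal approximation gives 63 per group for 0.50 SD at 80% power. The exact noncentral t gives power 0.795 at 63 and 0.801 at 64. The stated 64 per group is reproduced.

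**Step 2: power within a half.** With 32 per arm, power at 0.50 SD is 0.504. With 35 per arm it is 0.541.

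**Step 3: chance that exactly one part is significant.** With powers p1 and p2 in the two parts,

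P(discordant) = p1(1 − p2) + p2(1 − p1).

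- Equal halves, 64 per group: 2 × 0.504 × 0.496 = 0.500.
- Equal halves, 70 per group: 2 × 0.541 × 0.459 = 0.497.
- 80/20 split, 64 per group: 0.707 × 0.771 + 0.229 × 0.293 = 0.61.

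The same formula over a range of true common effects gives:

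| True effect (SD) | Halves, 64/group | Halves, 70/group | 80/20, 64/group | 80/20, 70/group |
|---|---|---|---|---|
| 0 | 9.5% | 9.5% | 9.5% | 9.5% |
| 0.2 | 21.7% | 22.7% | 22.2% | 23.3% |
| 0.4 | 45.5% | 47.0% | 51.2% | 53.6% |
| 0.5 | 50.0% | 49.7% | 61.3% | 62.5% |
| 0.6 | 45.1% | 42.3% | 63.6% | 62.7% |
| 0.8 | 20.7% | 16.4% | 50.7% | 47.0% |

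Baseline adjustment in the MMRM changes little. With an assumed baseline correlation of 0.5 the effective difference is 0.5/√(1 − 0.25) = 0.577 SD, and discordance for equal halves is 0.470 (64 per group) or 0.447 (70 per group).

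**Step 4: four variables, like for like.** Simulation of 8,000 trials per scenario, with four independent binary variables of about equal halves and no true difference between sub-groups:

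| True effect, n/group | Discordant, per variable | Discordant, any of 4 | Interaction p < 0.05, per variable | Interaction p < 0.05, any of 4 |
|---|---|---|---|---|
| 0.50 SD, 64 | 51.0% | 81.5% | 5.2% | 19.2% |
| 0.50 SD, 70 | 49.8% | 79.8% | 5.0% | 18.4% |
| 0, 64 | 9.5% | 25.2% | 4.8% | 18.0% |
| 0, 70 | 9.1% | 24.3% | 5.0% | 18.5% |

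The last column agrees with 1 − 0.95⁴ = 0.185.

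**Step 5: what an interaction test can detect.** With two equal halves, each has n/2 per arm. The variance of the treatment difference in a half is 4/n in SD² units, and that of the difference between halves is 8/n.

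- 64 per group: SE = √(8/64) = 0.354. Detectable with 80% power: (1.96 + 0.842) × 0.354 = 0.99 SD. Power for a 0.5 SD interaction: Φ(0.5/0.354 − 1.96) = 0.29.
- 70 per group: SE = √(8/70) = 0.338. Detectable: 0.95 SD. Power for 0.5 SD: 0.32.

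**The case against.** The strongest reply is that the article never says sub-group results will be compared by significance, and never excludes an interaction. Its stated purpose, to see whether effects differ, is what an interaction serves. The same variables are already in the MMRM, a journal article condenses, and model terms and decision rules are commonly left to the promised SAP. Much of this stands. A reader might infer that the plan has committed to a significance comparison; the text does not support that, and the figures above hold only if such a comparison is made. What remains is that the article does name a method for this question, and in ordinary usage that method does not answer it. That is more than a detail left open.

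Three further readings are tempting but unsupported:

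- That false differences arise about half the time in general. The rate depends on the true effect and the split, neither of which the document gives.
- That t-tests and chi-squared tests are planned within sub-groups. The sentence naming them follows the sub-group sentence but refers to the primary and secondary outcomes, without tying the tests to sub-groups.
- That the policy conclusion would be misdirected. The main claim rests on overall superiority, and the main Discussion assigns part of the question of who benefits to an interview-based process evaluation.

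It is also fair to say that interaction tests in a trial of this size are weak. Step 5 confirms it.

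**Conclusion.** The point holds in a conditional form. The named method does not, on its natural reading, test whether effects differ. If within-group results were compared by significance, the chance of a spurious contrast for each variable would be about 50% at the trial's own design effect with equal halves, about 22% at 0.2 SD, about 10% with no effect, and 61-63% for an 80/20 split at 0.50 SD. For any of four independent binary variables at 0.50 SD it would be about 80%, against 18-19% with interaction tests. All of these assume a uniform true effect. The matter is worth correcting because the abstract presents the question of who benefits as a product of the trial, but it does not touch the primary comparison.

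**What to change.** Replace the sub-group sentence, in the SAP or a protocol update issued before the database is opened, with wording such as:

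> Whether the treatment effect varies with age, gender, educational level and duration of unemployment will be assessed, one variable at a time, by a treatment-by-time-by-variable interaction in the full-sample MMRM, reported as an estimate with 95% CI. These analyses are exploratory. Estimates within sub-groups are descriptive only.

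This also closes the list at the four named variables. Keeping age and duration continuous is preferable, since it avoids choosing cut-points, but it is optional.

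The cost is a change of wording and an extra model term; no new data are needed. The price in interpretation should be stated with it: power for a 0.5 SD interaction is about 29-32%, the interaction detectable with 80% power is about 0.95-1.0 SD, and a non-significant interaction is therefore no evidence that effects are equal. Any statement about who benefits becomes explicitly exploratory.

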### Methods: monitoring

#### Data monitoring

A data monitoring committee is not feasible for this trial due to its short duration and size. The researcher will have sole access to the data and will monitor it monthly to ensure that the quality of data is maintained throughout the trial. Furthermore, within the context of this trial, an interim analysis is not practicable as sufficient data may not be available at the interim point for analysis. However, the researcher through monitoring of the data will inform the NGO, should any issues arise with the data collection, the recruitment of participants or the implementation of the intervention. This is of particular importance due to the ongoing changes in LMP implementation in Ireland and its very real bearing on the trial progress. Nevertheless, the flexibility of the NGO will ensure that should any changes to the trial be required, they will within reason be facilitated.

#### Harms

There are some (minimal) risks envisaged in this study. From the researcher’s experience of working with job-seekers, there can be a tendency for the client to disclose personal information that may not be sought within the interview/focus group and to express their own experiences, difficulties and barriers and expect that the researcher may be able to offer further assistance. In practice, this involves setting and recognising clear boundaries while still providing an open and supportive environment within which the participant can engage in the interview/questionnaire completion.

Completion of the GHQ-12 may cause some minor distress, but the researcher is an experienced administrator of this measure and other similar questionnaires, as well as having well developed test administration skills. Close adherence to the British Psychological Society Code of Good Practice for Psychological Testing and the Psychological Society of Ireland Code of Ethics will also ensure that any risk will be managed according to best practice. If the client has a negative reaction to the administration of the questionnaires, a referral to an experienced guidance officer (i.e. the client’s case worker) in the DSP/NGO and the primary healthcare team will be made. In addition, information on a range of support services will be given to the client.

Other potential risks will be addressed by ensuring that there is appropriate local information pertaining to support services available. Such services include counselling services, addiction services, Local Employment Centre services and other community-based services. The researcher’s own training as a psychologist and experience of working with numerous disadvantaged clients will also ensure that each participant is treated with respect and that any signs of distress will be appropriately identified and the participant referred immediately to a suitable service(s).

Questionnaires will be administered in the NGO, which has, through its own Health and Safety policy, procedures in place regarding the safety of clients and staff. These procedures will be followed alongside the National University of Ireland Maynooth, Department of Psychology guidelines ‘Guidance for safe working practice in psychological research’.

Further to the protection afforded by the above policies and guidelines, participants will be provided with a detailed and easily comprehensible information sheet and an informed consent sheet (see Additional file 3) and will be reminded of their option to withdraw from the study at any time (up until the point of data analysis) should they so desire.

#### Auditing

Auditing will not be necessary in this study due to its short duration.

### Ethics and dissemination

#### Protocol amendments

Should any amendments to the protocol be required, particularly those which may impact the trial and its implementation or the participants and their outcomes, a formal amendment to the protocol will be required. This will necessitate approval from the funder, the NGO and the National University of Ireland Maynooth Social Research Ethics Committee. Administrative amendments which do not impact on the trial and participants will not require formal approval, but will be documented by the researcher in the tracking file.

#### Consent or assent

Consent is sought from participants involved in the study at the first meeting with the researcher. Each participant is provided with an information sheet (Additional file 3) outlining the background to the study, the rationale and the objectives. Participants also receive a consent form (Additional file 3) which they are asked to sign; a copy is given to them to retain for their own records. The researcher also talks through both documents to ensure they are properly understood by the participants. Verbal consent will be sought if any issues regarding poor literacy arise.

All participants in this study who may be considered potentially vulnerable are in receipt of a Job Seekers payment, thereby deeming them fit for employment. It is likely, therefore, that participants are capable of consenting to participation. However, assent is also sought on occasions where the researcher has concerns regarding the participant’s understanding of the process. The researcher also talks through both the information sheet and the consent forms to ensure they are properly understood by the participant.

As this study requires participation on more than one occasion, participants will be contacted before the follow-up assessment (post intervention and six-month follow-up) and continued consent will be sought before the follow-up study commences. Again, a copy of the consent form will be given to participants as soon as possible after consent has been obtained. If the participant does not wish to continue, they may withdraw at any time. Completion of the withdrawal slip which forms part of the information sheet will be requested for the researcher’s records. Data can/will be withdrawn up until the point of completion of data entry. Consent and continued consent are sought solely for this study as no ancillary studies are planned.

Participants are informed in the information sheet of the ongoing nature of this study and will be informed throughout of their right to withdraw participation up until the point of data entry without penalty. As this study is closely linked to the services provided by the Department of Social Protection, participants may have concerns that non-participation may have a negative effect on their social welfare payment. The information sheet and the informed consent form clearly indicate that there is no conditionality related to this study and that no penalties apply for non-participation. Furthermore, participants are informed that they may, at any time, contact the researcher should they have concerns regarding their participation. Participants are also informed by email/post when each aspect of the study relating to their participation is complete and may request a summary of the research findings when it becomes available.

#### Confidentiality

All identifying information is removed from the data in order to protect the safety and integrity of the research participants. Each participant is allocated a unique identifier at the point of consent and is informed of this in the consent form. A document (encrypted and password-protected) containing the coding key is only accessible by the researcher and is located on a removable storage device in a locked filing cabinet in the researcher’s office.

All coded data are stored on the researcher’s computer and protected by encryption software (McAfee Endpoint Encryption), and backed up every week on a separate removable storage device (also encrypted) which is stored safely in the researcher’s office. The coding key and electronic raw data will be held securely for a minimum of ten years after completion of the study, after which they will be destroyed.

In addition, the information sheet alludes to the fact that: (1) this study will be published and the key findings presented at conferences and other public fora; (2) that all identifying information will be removed at the point of consent; and (3) that nobody will be identified in any publications.

Participants are also made aware that there may be instances where the researcher cannot maintain confidentiality, for example, where participant’s safety or wellbeing, or indeed the safety of others is at risk, and that a referral to the relevant services (e.g. mental health service) may be required.

#### Access to data

The researcher, authors and the NGO will be given access to the cleaned dataset at the end of the study. The dataset will be password-protected and will be housed on a server in the NGO. The anonymised data will be made publicly available, as required by registration with the ISRCTN and upon request to the NGO.

#### Ancillary and post-trial care

Participants will be provided with post-trial care in the form of referral to ancillary services, such as primary healthcare, including mental health, counselling services, addiction services, local employment services and other appropriate community-based services, should they be required. The researcher and practitioners implementing the intervention or usual service will monitor participants’ responses to the services, and in the unlikely event that concern for a participant arises, particularly in terms of negative or adverse impacts stemming from their participation in the trial, a referral will be made immediately to a suitable service(s).

Should this study provide evidence of the effectiveness of the EEPIC intervention in improving wellbeing and employability, participants who do not receive the intervention (but who receive the PTWP service) may receive the intervention at a later point if agreed by the DSP. The researcher will make a strong recommendation to the NGO and to the DSP, that those who participated in the control group be offered this service as soon as possible.

#### Dissemination policy

Trial results will be disseminated to participants, employment services, relevant government departments and other interested organisations (e.g. charities, social justice organisations, community-based services). Findings will also be presented at appropriate academic conferences and seminars and published in peer-reviewed journals and on relevant websites (e.g. the NGO website). As indicated above, the trial has been registered with ISRCTN, and has been promoted at community level, and with wider employment services and the DSP. A summary report of the findings will be prepared for the NGO and recommendations made for policy and practice. In addition, a number of academic manuscripts are anticipated: (1) a paper on the major outcomes from the study; and (2) a paper detailing specific aspects of the study. The authors of these papers will be those listed as the protocol contributors. Anonymised data will be made publicly available through the Irish Social Sciences Data Archive (ISSDA) and the Irish Qualitative Data Archive (IQDA) as required by registration with the ISRCTN. This will be available within six months of the trial end date.

